**7.0 Data management**

A detailed database will be developed to track each participant’s progress and will include notes on any clinical or study deviations. All study data will be stored in encrypted files on secure servers at the University Health Network and outcome data will be stored on REDCap® which is a secure web-based application for electronic data. Data files will be restricted to study investigators and authorised study personnel. Data quality and integrity will be assured using data audits, access control, and monitoring and cleaning data.

**8.0 Analyses**

**8.1 Primary outcome**

Study feasibility will be evaluated using descriptive statistics and will include: 1) the rate of recruitment (average number of patients per month) 2) the number and proportion of patients who are eligible (and reasons for ineligibility); 3) the number who provide consent (and reasons for declining); 4) attrition rates at each time point (and reasons for drop out); and, 5) capture of outcome data at each time point and missing items. The feasibility of the intervention will be assessed by examining: 1) Fitbit^TM^ and Physitrack usage; and 2) Weekly virtual check-in attendance.

Acceptability will be assessed qualitatively through the interview data and a thematic analysis will be conducted^119^. Analyses will be primarily deductive with a number of categories pre-selected to align with the main program components as well as program strengths, weaknesses, and areas of improvement. Once this initial coding is complete, the interviews will be read once again, and any additional codes will be derived inductively. Themes will be generated by a close examination of codes and categories, and the relationships between them, and discussions with the research team.

Any safety event related to the program will be reported using Common Terminology Criteria for Adverse Events v5.0^9^ .

**8.2 Secondary Outcomes**

Capture rates of the patient-reported outcomes will be assessed and described at each time point overall and for each treatment arm to inform future sample size calculations. The distribution of baseline values (mean/standard deviation and median/interquartile range) will be summarised for all outcomes. To inform sample size calculations for a phase I trial Within-person change from baseline to follow-up (T3-T1) will be calculated and summarised for all outcomes. To understand how Ex-CIPN affects change, mixed effects models will be used to estimate the change from baseline to post-intervention and from post-intervention to follow-up using all available data for each patient (allowing us to incorporate data from patients who withdraw from the study). Separate models will be run for each of the secondary outcomes to provide information about the magnitude and timing of change for each outcome. Data will be analyzed when all recruitment and data collection has been completed.

**9.0 CRITERIA FOR POSITIVE TRIAL/Interpretation of Results**

We will define our intervention as feasible to test in a larger, multi-center RCT if there is reasonable recruitment of 4-5 participants per month^7,122^, retention of 70% at each time point ^7,72^ and reasonable adherence (70%) to the intervention components (including Fitbit usage, call attendance, and completion of weekly exercise plans)^7^. In addition, success will be measured by high levels of treatment acceptability based on survey and qualitative interview data. Safety of the intervention will be confirmed if no serious adverse events (defined as anything above a Grade 2 of the CTCAE v5) related to participation in the intervention occur. If any one of those criteria is not met, we will make appropriate modifications to the protocol prior to a larger RCT. Calculation of the sample size for a larger RCT will be based on a minimally important clinical difference of 2 points between the T1 and T3 on the numeric pain rating scale^111^ .

# **10.0 Data Collection, Handling, and Storage**

**10.1 Data Collection**

Study data will be collected from patient-reported outcomes/ questionnaires and/or participant’s medical records, and transcribed on case report forms (CRFs). These forms can be paper, electronic, or both. The medical records will be reviewed at study-specific timelines/visits for the collection of results from routine clinical tests that are carried out as part of standard of care.

Study data will be under secure password or kept under lock and key in the research office.

**10.2 Data Handling**

Patient registration and outcomes reporting will be through a de-identified database web-based accessible for registered investigators through research database (REDCap). The research database provides an environment for collecting, managing and reporting outcome data and enables the flexibility to meet the unique requirements of this study. The application also provides an extensive administrative interface, with capabilities to create, design and manage clinical research forms. Furthermore, it is fully compliant with privacy regulations (HIPAA/PIPEDA), with enhanced privacy-related features including audit logging capabilities, role-based user access permissions, and a repository for study-related source documentation. Any source documents that contain Personal Health Information (PHI) will be properly de-identified prior to being uploaded to the research database.

Hard copy study files will be kept secured. All computerized files will be password protected. Coded study data will be stored on research servers.

**10.3 Storage and Record Retention**

Study data will be stored and archived as follows:

1. Hard copies: consent forms, questionnaires, coordinator source documentation
2. Electronic data: medical records (EPR/EPIC), images (Coral viewer, PACS), all other data (RMP network), regulatory files

In accordance with institutional policies, all records and documents pertaining to the study will be retained by the study trial site for 10 years from the completion of the study, and will be available for inspection by institutional representatives (e.g. REB, CCRU Quality Assurance), sponsor, Health Canada, and other regulatory bodies. No clinical trial records will be destroyed without the documented consent of the PI.

**10.4 Data Safety and Monitoring Plan**

The PI will assume primary responsibility for monitoring the progress of the trial and the safety of participants.

As part of UHN-PM, this trial may be selected at random to be monitored by the staff of the data safety and monitoring board. Data will also be submitted to the UHN REB annually for continuing review and at the completion of the study.

# **11.0 Ethics**

**11.1 Research Ethics Board (REB)**

The study will be submitted for initial and ongoing annual REB review at the University health Network (Panel C). Study related procedures will not commence prior to receipt of REB approval. All study protocols, consent forms, and patient-facing material will receive REB approval before being used. Any amendment to the study will be submitted for review by the REB before any changes are implemented unless required to eliminate immediate hazard to the study participants.

**11.2 Informed Consent Process**

If a potential participant has expressed interest in the study, a qualified study team member will discuss the study details and consent form with the potential participant either in-person or remotely (e.g. telephone, MS Teams). This discussion will involve careful explanation of all items outlined in the consent form, the investigational nature of the study, any benefits and risks to research participants. Sufficient time will be given to the potential participant to answer any questions.

Written informed consent will be obtained prior to the participant beginning any study-related procedures.

If new information becomes available during the study, study participants will be informed of the changes and asked to re-consent by study staff, if required.

**11.2.1 REDCap eConsent**

If in-person consenting is unavailable, then remote consenting can be completed using the UHN Approved REDCap eConsent Process. Potential participants will be contacted via telephone to conduct the informed consent discussion. A standard script will be used to ensure the same process is followed for every participant. After all the participant’s questions have been answered, they will be sent a REDCap link via email. A member of the research team will assist the participant when completing the eConsent form.

**11.3 Protocol Deviations**

A protocol deviation is any noncompliance with the clinical trial protocol and/or Good Clinical Practice (GCP). The noncompliance may be either on the part of the subject, the investigator, or the study site staff. The study PI and study staff are responsible for knowing and adhering to the study protocol and the reporting requirements of relevant regulatory agencies (e.g. UHN REB). In the event a deviation occurs, the details and reason(s) for the deviation, as well as any effect on patients’ safety and/or trial data, must be documented. All deviations from the protocol will be addressed in study subject source documents. Corrective and preventative actions will be developed by the site and implemented promptly. If the deviation meets the reporting requirements of the relevant regulatory agencies, the deviation will be reported in a timely manner. These practices are consistent with ICH E6.

#

# **12.0 Direct Access to Source Data/Documents**

- Only the investigators and the study team will have access to study-related source data/documents.
- The link of study number and identifiable information (e.g. Medical Records Number) will be stored separately from the remainder of the study information and not be transported or transmitted outside the research office.

# **13.0 Publication and data avaiLability Policy**

Data derived from this study may be reported in scientific publications. Patients will not be indicated by name in any publications or presentation that may result from this study. Study data will be available upon request (following REB approval).

# **14.0 Time to Study Initiation and Milestone Achievements**

| **Objectives** | **Milestones** | **Start Date** | **Completion Date** | **Describe how you are going to monitor progress (Deliverables)** |
| --- | --- | --- | --- | --- |
| Develop research protocol | Completion of study design and protocol | April, 2023 | Sept, 2023 | Completion of one clinical trial research protocol |
| Obtain Research Ethics Board (REB) approval | REB submission and approval | Oct 2023 | Jan 2024 | Receipt of approval by REB at PM |
| Register the clinical trial and publish study protocol | Registration of the clinical trial on ClinicalTrials.gov  Manuscript completion, submission, acceptance. | Nov 2023 | Feb 2024 | ClinicalTrials.gov posting  Protocol article published |
| Train research staff | Training Rkin to deliver intervention and MSc student to run study | Nov 2023 | Feb 2024 | Good Clinical Practice (GCP) and relevant technical training certificates of research staff |
| Initiate the trial | Activation of trial | Feb 2024 | Feb 2024 | First patient enrolment |
| Monitor trial accrual | Completion of trial accrual | Dec 2023 | Mar 2025 | Completion of 50% of total target accrual by Aug, 2024.  Completion of 100% of total target accrual by Mar, 2025. |
| Complete follow-up data collection | Data collection completion | Apr 2024 | Aug 2025 | Completion of 50% of follow up data collection by Jan, 2025.  Completion of 100% of follow up data collection by Aug, 2025. |
| To report/ disseminate trial results in a timely manner | Abstract submission and presentation | Sept 2025 | Dec 2025 | Conference abstract publications submitted for 1 national, and 1 international meeting with patients, healthcare providers, and/or relevant stakeholders in the audience. |
| To publish trial results | Manuscript completion, submission, and acceptance. Reporting of results on ClinicalTrials.gov. | Sept 2025 | Dec 2025 | One article published ClinicalTrials.gov results posting. |

| Acceptability | Surveys for all study participants | qualitative, not pre-defined |  |  |  |
|  | Semi-structured qualitative interview will explore participants experience in EX-CIPN (INT only) | qualitative, not pre-defined |  |  |  |
|  |  |  |  |  |  |
| Data completion rates | Number (%) of assessed participants reporting each outcome at T2 and T3 |  |  |  |  |
| **Secondary Outcomes** |  | **not applicable** |  |  |  |
| Pain (Primary clinical outcome) | Numeric Pain Rating Scale |  |  |  |  |
|  |  |  |  |  |  |
| CIPN Symptom severity | EORTC CIPN-20 |  |  |  |  |
|  |  |  |  |  |  |
| CIPN-related Disability | CIPN-RODS |  |  |  |  |
|  |  |  |  |  |  |
| Quality of Life | EORTC-QLCC30 |  |  |  |  |
|  |  |  |  |  |  |
| Physiological factors |  |  |  |  |  |
| -          Upper body strength | Grip dynamometer |  |  |  |  |
| -          Lower body strength | Sit to Stand Test |  |  |  |  |
| -          Balance | Berg Balance Test |  |  |  |  |
| -          Fitness | 6MWT |  |  |  |  |
| -          Gait speed | Gait speed test |  |  |  |  |
|  |  |  |  |  |  |

#

# Analysis of Secondary Outcomes

The following mixed effects model will be fit to estimate the outcome of participant $i$ at time $t$ the secondary outcomes:

$$y_{it}=\beta_{0}+u_{0i}+\beta_{1}T_{2i}+\beta_{2}T_{3i}+\beta_{3}T_{2i}x_{i}+\beta_{4}T_{3i}x_{i}$$

Where:

- $\beta_{0}$ is the average baseline ($T_{1}$) value and is assumed to be equal between groups due to randomization
- $u_{io}$ is a random baseline effect and assumed to be normally distributed across participants
- $T_{2i}$ and $T_{3i}$ are dummy-coded time indicators to enable estimation of the treatment effect after intervention ($T_{2}$) and at follow-up ($T_{3}$), respectively.
- $x_{i}$ is the treatment allocation of participant $i$
- $\beta_{1}$ and $\beta_{2}$ are the time effects evaluated at $T_{2}$ and $T_{3}$, respectively
- $\beta_{3}$ and $\beta_{4}$ are the intervention effects evaluated at $T_{2}$ and $T_{3}$, respectively

Data Structure:

| ID | Time | Group | x | T2 | T3 |
| --- | --- | --- | --- | --- | --- |
| 1 | T1 | Control | 0 | 0 | 0 |
| 1 | T2 | Control | 0 | 1 | 0 |
| 1 | T3 | Control | 0 | 0 | 1 |
| 2 | T1 | Intervention | 1 | 0 | 0 |
| 2 | T2 | Intervention | 1 | 1 | 0 |
| 2 | T3 | Intervention | 1 | 0 | 1 |

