**Study Design**

The proposed study is a single centre single-group Phase I trial with patients who are experiencing persistent CIPN. All participants will receive the EX-CIPN intervention. EX-CIPN is comprised of: a progressive 10-week exercise program (aerobic, resistance and balance) supported with a mobile application (Physitrack^®^) and wearable technology (Fitbit™) to track activity; and (2) weekly brief video/telephone check-ins provided by an oncology exercise specialist who is trained in motivational interviewing. Informed by behavior change theory, the program components aim to provide patients with the knowledge and tools needed to reach and maintain their wellness and exercise goals. The remote delivery of EX-CIPN helps to barriers to accessing and providing rehabilitation and provides a cost-effective model that can be widely adopted. There will be three assessment time points throughout the study (T1, T2, T3) all including patient reported outcomes and a physiologic assessment. T1 is a baseline assessment before the intervention begins, T2 is a post-intervention assessment, and T3 is a 3-month follow-up after intervention completion.

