***Primary Endpoints:***

**Primary Endpoint 1: *To determine if EX-CIPN is feasible (retention and adherence), acceptable, and safe in cancer survivors experiencing persistent CIPN.***

**Primary Endpoint 2: *To examine the feasibility of the study design and methods (accrual and retention rates, feasibility of data collection and procedures).***

- Recruitment and accrual will be tracked based on CONSORT criteria^93^ through a screening log that tracks data collected from all referred and screened patients. Eligibility screening will be performed to identify eligible, consented, and eligible non-recruited individuals with non-recruitment reasons documented.

*We will define our intervention as feasible if we are able to accrue an average of five (5) participants per month.*

- Retention rates at each study time point will be monitored. Retention rates will be calculated as the proportion of recruited participants that attend each assessment time point (T1, T2, and T3). We will also examine rates of complete and missing data.

*We will define our intervention as feasible to test in a subsequent RCT if there is reasonable retention (>70%) at each study time-point, in both arms****.***

- Adherence to the intervention will be assessed through health coaching call attendance, Fitbit™ usage, and self-report completion of weekly exercise plan (determined during weekly calls).

*We will define our intervention as feasible to test in an RCT if there is reasonable adherence (>70%) to the intervention components (including Fitbit usage, call attendance, and completion of weekly exercise plans).*

- Safety will be assessed throughout the study. All adverse events will be scored on the CTCAE version 5.0 ^9^ and documented during weekly appointments and at follow-up assessments with the RKin.

*Safety of the intervention will be confirmed if <10% of participants experience serious adverse events (defined as anything above a Grade 2 of the CTCAE v5) related to participation in the study or intervention occur.*

- To evaluate acceptability and guide future program refinement, we will ask all participants to complete a post-study survey immediately after T2 to provide feedback on their experience. We will also conduct in-depth semi-structured qualitative video interviews (MS Teams) with a sub-sample of approximately 1/3 of participants following the T2 assessment (including those who improved in CIPN symptoms and those who did not improve).

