***Secondary Endpoints***

**Secondary Endpoint 1: Reduction in the patient-reported CIPN-related pain (primary clinical outcome) will be summarized in the intervention and control groups.**

*Calculation of the sample size for a larger RCT will be based on distribution of change observed in this pilot and a minimally important clinical change of 2 points on the numeric pain rating scale from T1-T3 assessment.*

Secondary Endpoint 2: Estimates of the effect of the EX-CIPN intervention on CIPN symptoms, CIPN-related disability and physiologic outcomes including upper and lower body strength, balance, gait speed, and functional capacity (exploratory secondary outcomes).

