**4.0 Study Intervention AND Procedure**

**EX-CIPN**

All participants will receive the EX-CIPN intervention. EX-CIPN has been developed based on previous evidence and guidance regarding CIPN and exercise^6,71-75,83^, exercise guidelines for cancer survivors, and established behaviour change theory and techniques to promote uptake of behaviours^77-82^. The remote delivery of EX-CIPN helps to barriers to accessing and providing rehabilitation and provides a cost-effective model that can be widely adopted. EX-CIPN is comprised of: a progressive 10-week exercise program (aerobic, resistance and balance) supported with a mobile application (Physitrack^®^) and wearable technology (Fitbit™) to track activity (see Table 2 for specific exercise components); and (2) weekly brief video/telephone check-ins provided by an oncology exercise specialist who is trained in motivational interviewing. Informed by behavior change theory, the program components aim to provide patients with the knowledge and tools needed to reach and maintain their wellness and exercise goals (see Table 3  for list of embedded behavior change techniques and tools^99^). Multiple theoretical models are integrated within the intervention (i.e., motivational interviewing, cognitive behavioral therapy, transtheoretical model of behaviour change), with the focus on addressing and resolving motivational ambivalence and identification and modification of the cognitive distortions that prevent adoption of appropriate health behaviors and addresses relapse and long-term maintenance of behavior change^77-82^. The program is provided free-of-charge to participants, other than out of pocket travel costs (i.e., public transport, parking) for in-hospital assessments.

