**6.0 Sample Size and timeline**

While there is no overall consensus regarding appropriate sample size in a feasibility study^115^, based on a simulation of a range of sample sizes and values of standard deviation for precision of estimate (α=0.05 and power at 80%); 35-40 is at the elbow point of the curves (see Figure 3). Therefore, a sample size of 40 participants will be included in the study, which is considered large enough to examine the feasibility of the study^116,117^.

There are approx. 400-500 cancer patients who receive either platinum or taxane-based curative/(neo)-adjuvant chemotherapy per year at the Princess Margaret Cancer Centre per year. It is estimated that 30-40% of these patients will report CIPN > 6 months post-treatment^21^. Based on this, we anticipate recruiting 5-6 participants per month (See Figure 4). The study will take 15 months for accrual and 20 months for data collection.

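### The secondary-outcome mixed model is left over from a randomised two-arm design; in this single-group trial its intervention-effect coefficients cannot be estimated

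*Protocol*

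**What the plan says.** The design is stated plainly. The Synopsis and Section 3.1 say: "The proposed study is a single centre single-group Phase I trial with patients who are experiencing persistent CIPN". Section 4.0 adds: "All participants will receive the EX-CIPN intervention". Section 6.0 fixes the size: "Therefore, a sample size of 40 participants will be included in the study".

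The appendix headed Analysis of Secondary Outcomes prints a model for a different design. The outcome is a fixed intercept β0, a random intercept, time indicators T2 and T3 (β1, β2), and the products T2·x and T3·x (β3, β4). Here x is the participant's treatment allocation. The baseline mean is a single parameter "and is assumed to be equal between groups due to randomization". β3 and β4 are defined as the intervention effects at T2 and T3, and the example data table has one Control participant (x = 0) and one Intervention participant (x = 1).

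Section 8.2 describes something else for the same outcomes: mixed models for the change from T1 to T2 and from T2 to T3, with no group contrast. Yet it also wants capture rates "overall and for each treatment arm to inform future sample size calculations". Other two-arm remnants are Secondary Endpoint 1 in the Synopsis, where pain "will be summarized in the intervention and control groups", and the Synopsis retention rule, which asks for "reasonable retention (>70%) at each study time-point, in both arms". Sections 3.4 and 5.1 mention randomisation. In the outcome table after the references, the retention row counts randomised participants and the interview row is limited to an intervention arm.

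**The concern.** The appendix commits to a model whose key coefficients need a comparison group that the trial does not have. This is not detail left to a later analysis plan: the protocol itself prints the equation and defines the coefficients. It also leaves two incompatible analyses in place for every secondary outcome, one with a group contrast and one without.

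The stake is the label on the result. An analyst who has to make the model run must drop one of each duplicated pair of terms. Dropping the x terms leaves time effects; dropping the time terms leaves the same numbers under the name of intervention effects. The secondary objective (Synopsis and Section 1.2) already speaks of effects of EX-CIPN, and nothing in the protocol cautions that a single-arm change also contains natural change and regression to the mean.

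**Working it through.** **The plan's own figure.** Section 6.0 chooses 40 because, for "precision of estimate (α=0.05 and power at 80%); 35-40 is at the elbow point of the curves". This cannot be reproduced: the text gives no range of standard deviations and the figure is not shown. Nothing below depends on it.

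**Inputs.** 40 participants (Section 6.0); three visits, T1 to T3 (Section 5.2); x = 1 for everyone (Section 4.0, with the appendix coding Intervention as 1); model columns [1, T2, T3, T2·x, T3·x] (appendix).

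**Step 1: rows of the design matrix.** With x = 1, each participant contributes:

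| Visit | 1 | T2 | T3 | T2·x | T3·x |
| --- | --- | --- | --- | --- | --- |
| T1 | 1 | 0 | 0 | 0 | 0 |
| T2 | 1 | 1 | 0 | 1 | 0 |
| T3 | 1 | 0 | 1 | 0 | 1 |

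Column 4 equals column 2, and column 5 equals column 3.

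**Step 2: rank.** For 40 × 3 = 120 rows and 5 columns, the computed rank is 3. A 20/20 split of x gives rank 5, so the model is sound for the two-arm design it was written for.

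**Step 3: what can be estimated.** The null space is spanned by (0, 1, 0, −1, 0) and (0, 0, 1, 0, −1). A linear combination of coefficients is estimable only if it is orthogonal to both.

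- β0: products 0 and 0. Estimable.
- β1 alone: 1 with the first vector. Not estimable. β3 alone gives −1, and β2 and β4 give 1 and −1 with the second vector. None is estimable.
- β1+β3: 1 − 1 = 0. Estimable; the mean change T2−T1.
- β2+β4: 1 − 1 = 0. Estimable; the mean change T3−T1.

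The result is algebraic and holds at any sample size.

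**Step 4: fitting it.** On one simulated single-arm data set (n = 40), the model as written stopped with a singular-matrix error. Keeping only T2 and T3 gave −0.84 and −0.91. Keeping only T2·x and T3·x gave the same two values. The estimates are identical and only the name changes.

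**Step 5: illustration of the labelling risk.** Assume an SD of change of 2 points (not in the protocol), n = 40, no true exercise effect, and a natural drift of the size shown. The drift is returned in full as the estimate.

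| Assumed drift (points) | 95% CI excludes 0 |
| --- | --- |
| 0 | about 5% |
| −0.5 | about 35% |
| −1 | about 86% |
| −2 | about 100% |

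**Step 6: the model without x.** Columns [1, T2, T3] have rank 3 for 3 parameters, so every coefficient is estimable. The 95% half-width for a mean change, in units of the SD of change, is t(0.975, n−1)/√n. At n = 40 it is 0.32. At 70% retention (0.70 × 40 = 28) it is 0.39.

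**The case against.** The best defence is that Section 8.2 already gives a workable single-group analysis, and that its T2−T1 and T3−T1 changes are exactly the sums that remain estimable. No data are lost. Section 9.0 bases progression on recruitment, retention, adherence, acceptability and safety, none of which uses this model, and the outcome table sets no success criterion for secondary outcomes. The error also tends to show itself: the trial fit stopped and did not quietly return an answer. All of this stands. It limits the consequence, but the printed model still cannot be fitted as written and still contradicts Section 8.2.

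The size of any natural change is also unknown. Section 2.0 says acute CIPN generally improves over the first 3-6 months, and entry is at 6-12 months. The entry thresholds are on PRO-CTCAE numbness and tingling and on the DN4, not on the numeric pain scale, so regression to the mean in pain would be indirect. The drift values above are therefore illustrations, not forecasts.

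Four stronger readings are tempting, and the protocol does not support them.

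- From rank 3 of 5, a reader might infer that only two coefficients are lost. In fact all four of β1 to β4 are individually non-estimable, while the two sums survive.
- A reader might infer that the retention rule and Secondary Endpoint 1 cannot be evaluated. Both can be assessed in the one group that exists; the Synopsis defines retention as the proportion attending each visit, and Section 9.0 restates 70% without arms.
- A reader might add that a random intercept alone misstates the standard error of the T3−T1 change. That depends on visit correlations the protocol does not give. Section 8.2 summarises the T3−T1 change directly, and the covariance structure may be left to the SAP.
- A reader might say that misreporting will follow. It is a risk, not a certainty.

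**Conclusion.** The point holds. The appendix model contradicts the single-group design and the time-only analysis in Section 8.2, and the intervention effects it defines cannot be obtained from this trial at any sample size. The rank result rests only on x being the same for all participants, which the protocol states. Only the drift illustration needs outside assumptions (SD of change 2 points; drift 0 to −2 points). The reach is limited to exploratory secondary outcomes, whose within-person changes remain estimable; no feasibility or safety decision depends on the model. It should be corrected because the written specification is unusable and invites a causal label that a single arm cannot carry.

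**What to change.** In the appendix, delete x, β3, β4, the randomisation assumption and the Control rows of the data table. Replace the equation with

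y_it = β0 + u_0i + β1·T2 + β2·T3 + e_it,

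which also supplies the residual term missing from the printed equation. The within-person covariance may be left to the SAP. Report β1 (T2−T1), β2 (T3−T1) and β2−β1 (T3−T2, the second change named in Section 8.2) with 95% CIs. Call them within-person changes, and state that they include natural change and regression to the mean.

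Align the remaining two-arm wording:

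- Synopsis: the arms in the retention rule, and the control group in Secondary Endpoint 1.
- Section 8.2: the reference to treatment arms.
- Sections 3.4 and 5.1: randomisation.
- Outcome table: randomised participants in the retention row, and the intervention-arm restriction in the interview row.

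Reword the effects of EX-CIPN as within-person change in the Synopsis secondary objective, Secondary Endpoint 2 and Section 1.2.

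The cost is protocol text, one model specification and a slightly weaker secondary claim. No extra participants or data are needed.
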